### Sample size

2.2

Aligned with the study’s objective, Montreal Cognitive Assessment Scale (MoCA) was chosen as the primary outcome. According to the results of previous experiments and literature review (13, 14), the mean and standard deviation of MoCA scale in PD-MCI patients received acupuncture combined with anti-PD drug treatment were 25.32 and 4.34, while there were 21.48 and 4.44, respectively, in PD-MCI patients who received sham acupuncture combined with anti-PD drug treatment. PASS V.15.0 (NCSS, Kaysville, UT, United States) was used to calculate the sample size. We set 90% for power level and 5% for two-sided significance level. It was estimated that there were about 29 patients in each group, and considering the dropout rate of 20%, the total sample size needed for study is 72, with 36 patients in each group.

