### Outcome measure

2.6

General information of the participants, including name, age, sex, disease duration, education, Levodopa-equivalent dose, will be collected before the study begin. Primary outcome measure will be the Montreal Cognitive Assessment Scale (MoCA). The secondary outcome will be the Mini-Mental State Examination (MMSE), Unified Parkinson’s Disease Rating Scale Motor Examination (UPDRSIII), serum neurofilament light polypeptide (NfL) and serum glial cell-derived neurotrophic factor (GDNF). Serological indicators will be measured by enzyme-linked immunosorbent assay (ELISA). The schedule of the outcome measurements is shown in Table 2.

**Table 2 tab2:** Schedule of enrollment, intervention, assessment and safety.

Study period								
Time point (Week)	−1	0	1	2	3	4	5	25
Enrollment								
Eligibility screen	×							
Informed consent	×							
Randomization		×						
Allocation		×						
Intervention								
Acupuncture								
Placebo Acupuncture								
Assessments								
MoCA		×					×	×
MMSE		×					×	×
UPDRSIII		×					×	×
NfL		×					×	
GDNF		×					×	
Safety								
Vital signs		×		×			×	×
Adverse events			×	×	×	×	×	×

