### Follow-up

2.8

Patients will be followed up 6 months after the end of treatment. The outcomes scales will be assessed to evaluate the long-term efficacy of acupuncture.

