### Statistical analysis

2.10

In this study, IBM SPSS Statistics 26.0 statistical software will be used to analyze the collected clinical data. Shapiro–Wilk will be used to test the normality before statistical analysis. Counting data is expressed as a percentage using a chi-square test. The measurement data meeting the normal distribution will be represented by mean ± standard deviation, while those not meeting the normal distribution will be represented by quartile. The independent sample t test will be used to compare the two groups with normal distribution and homogeneous variance, and the Mann–Whitney U test will be used to compare the two groups with non-normal distribution. The comparison difference before and after treatment will be treated by paired sample t test with normal distribution, and Wilcoxon rank sum test with abnormal distribution. The two groups of repeated measurement data do not meet the normal distribution of the generalized estimation equation, the simple effect in the group will be analyzed by Friedman test. Two-sided test will be applied uniformly in this study, and *p* ≤ 0.05 will be the standard of statistical significance.

To evaluate the clinical relevance of the findings, we will perform a responder analysis based on the minimal clinically important difference (MCID) for the MoCA. Based on previous literature in cognitive impairment (21), a change of ≥1.22 points on the MoCA scale will be considered clinically meaningful. Participants who show an improvement of ≥1.22 points from baseline to post-treatment will be classified as ‘responders’. The difference in the proportion of responders between the study groups will be compared using a Chi-square test, with a *p*-value < 0.05 considered statistically significant.

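### The only sentence on repeated measures assigns a within-arm Friedman test, leaves the role of GEE unclear, and fixes no between-arm contrast for the long-term efficacy aim

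*Protocol article*

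**What the plan says.** Table 2 of the protocol article (section 2.6) schedules MoCA, MMSE and UPDRS III at weeks 0, 5 and 25. Section 2.8 gives the purpose of the last visit: "The outcomes scales will be assessed to evaluate the long-term efficacy of acupuncture".

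Section 2.10 contains two rules that bear on these data:

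- A general two-group rule. "The independent sample t test will be used to compare the two groups with normal distribution and homogeneous variance", and otherwise "the Mann–Whitney U test will be used to compare the two groups with non-normal distribution". Neither clause is limited to a particular visit.
- A repeated-measures sentence in two parts: "The two groups of repeated measurement data do not meet the normal distribution of the generalized estimation equation", followed by "the simple effect in the group will be analyzed by Friedman test".

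Section 2.2 sets 29 patients per group, raised to 36 after "considering the dropout rate of 20"%.

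**The concern.** The repeated-measures sentence has three faults in what it states.

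1. Read literally, it makes a normal distribution a property or condition of GEE. GEE needs a correct mean model and enough clusters for its robust errors; it does not need normal outcomes.
2. It does not parse, so two competent analysts could act on it in opposite ways: one would abandon GEE for non-normal data, the other would use GEE because the data are non-normal.
3. The only test it assigns is Friedman's test within a group. That test asks whether one arm's scores differ between visits. It yields no group-by-visit term and no estimate against sham, and it needs a complete set of visits from each patient.

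The non-normal branch may well be reached. The scales are integer-valued, and entry restricts MoCA to 18–25 and MMSE to 21–26, so a Shapiro–Wilk rejection is plausible.

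At stake is the reading of the follow-up visit. With a t test, Mann–Whitney, GEE and within-arm Friedman all available for one efficacy claim, the choice could be made after the data are seen.

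**Working it through.** **Step 1: the plan's own figure.** Section 2.2 gives means 25.32 and 21.48 and SDs 4.34 and 4.44.

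- Difference: 25.32 − 21.48 = 3.84.
- Pooled SD: √[(4.34² + 4.44²)/2] = 4.39. Standardised difference: 3.84/4.39 = 0.875.
- A two-sample t test at 5% two-sided with 90% power needs 28.46, so 29 per group, as stated.
- Dropout: 29/0.8 = 36.25, against the stated 36 per group. The difference is rounding.

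The planned size therefore rests on a between-arm comparison of means. It also supplies two inputs for step 3: 29 per arm and SD 4.39.

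**Step 2: which question each named method answers at week 25.**

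| Method in section 2.10 | Compares acupuncture with sham? | Adjusts for baseline? | Tied to week 25? |
|---|---|---|---|
| t test / Mann–Whitney U | yes | no | no |
| GEE, if used | could, through group × visit | not stated | no |
| Friedman in the group | no | not applicable | no |

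**Step 3: what within-arm verdicts would be worth, if they were used as evidence.** Assumptions: no true arm difference; both arms gain the same amount by week 5 and keep it at week 25; normal scores rounded to integers with mean 21.5 at baseline; Friedman in each arm at 0.05. The SD runs from 2.5 (an assumption; the narrow entry range makes a smaller value arguable) to 4.39 (section 2.2). The between-visit correlation of 0.5 to 0.8 is assumed. Let *p* be the chance that Friedman is significant in one arm. The arms are independent, so

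P(significant in the acupuncture arm only) = *p*(1 − *p*), which cannot exceed 0.25.

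Simulated *p* for a common 1-point gain (20,000 trials per row):

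| SD | Correlation | *p* | *p*(1 − *p*) |
|---|---|---|---|
| 2.5 | 0.5 | 0.47 | 0.25 |
| 2.5 | 0.6 | 0.56 | 0.25 |
| 2.5 | 0.7 | 0.70 | 0.21 |
| 2.5 | 0.8 | 0.87 | 0.11 |
| 4.39 | 0.5 | 0.17 | 0.14 |
| 4.39 | 0.6 | 0.20 | 0.16 |
| 4.39 | 0.7 | 0.265 | 0.19 |
| 4.39 | 0.8 | 0.377 | 0.23 |

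Sensitivity to the gain:

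- No gain: *p* ≈ 0.05, so 0.05 × 0.95 ≈ 5%.
- 2 points at SD 2.5: *p* = 0.975 at correlation 0.5, giving 2%; 0.993 at 0.6, giving 0.7%; practically zero above that.
- 2 points at SD 4.39: *p* runs from 0.56 to 0.935, giving 25% down to 6%.

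For comparison, Mann–Whitney on the change from baseline to week 25 (SD 4.39, common gains of 1 to 2 points) rejected in 4.5% to 5.2% of trials, as it should.

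**Step 4: patients lost to Friedman.** 0.20 × 72 = 14.4, so about 14 patients would be dropped if the whole sample-size allowance became a missed visit. The protocol does not state a week-25 missingness rate.

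**Step 5: what baseline adjustment adds.** At correlation ρ with baseline, an adjusted comparison has about 1 − ρ² of the variance of an unadjusted comparison of follow-up scores: 0.75 at ρ = 0.5 and 0.36 at ρ = 0.8.

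**The case against.** A reader might infer that week-25 efficacy will be judged without comparing the arms. The text does not support this. The t test and Mann–Whitney clauses compare the two groups without restriction to a visit, so they cover week 25. No sentence says that Friedman replaces them, or that durability will be inferred from significance in one arm and not the other.

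A reader might also take the false premise about GEE as settled. It is the literal reading, but not the only one. A simple effect is the usual name for a follow-up inside a group-by-time model, so the sentence may mean that non-normal data go to GEE, which compares the arms, with Friedman examining each arm afterwards. On that reading there is no false premise and no fallback.

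It is also tempting to quote the chance that exactly one arm is significant, about 50% at SD 2.5 and correlation 0.6. That counts sham-only results, which would not mislead in favour of acupuncture, and it rests on an SD that is not in the protocol.

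Finally, the 20% is an allowance for sample size, the handling of missing data may sit in an analysis plan that is not shown, and the sentence at most touches non-normal repeated data. All of this stands. It narrows the point but does not remove it: the sentence is wrong or ambiguous as printed, and on neither reading does it name the contrast that decides the long-term aim.

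**Conclusion.** The point holds as a defect of stated wording. Section 2.10 leaves it unclear whether GEE is used or abandoned, assigns only a within-arm test to the repeated measures, and ties no between-arm contrast to the long-term aim of section 2.8. A valid between-arm test at week 25 is available under the general rule, though unadjusted for baseline, so the week-5 primary comparison and its sample size are not undermined.

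The size of the risk is conditional. Only if within-arm verdicts were read as efficacy would an acupuncture-only result appear in roughly 11% to 25% of trials with no arm difference, given a common 1-point gain and the SDs and correlations assumed above. The figure moves strongly with the assumed gain and is not a predicted error rate for this trial.

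**What to change.** Replace the repeated-measures sentence with wording such as: *MoCA, MMSE and UPDRS III at weeks 5 and 25 will each be analysed in one linear mixed model with group, visit, group × visit and baseline value, using all observed visits of all randomised participants. For MoCA the week-5 group difference is primary. The week-25 group difference with 95% CI is the estimate of long-term efficacy. Friedman and paired within-arm tests are descriptive only.*

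GEE with an identity link and small-sample robust errors is an acceptable alternative. The mixed model is preferable if visits are missed, because it relies on a weaker missing-data assumption than ordinary GEE.

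The cost is a few lines of wording and slightly more analysis work. The mixed model can be fitted in SPSS 26, which the plan already names, and it uses only data already scheduled. The change should be made before unblinding.

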## Discussion

3

Parkinson’s disease with mild cognitive impairment (PD-MCI) is a primary non-motor symptom of PD. Recent studies have demonstrated widespread cognitive decline among PD patients, often accompanied by more severe depression compared to those without cognitive impairment (22). Additional research indicates that PD-MCI patients have a 39–59% probability of progressing to Parkinson’s disease dementia (PDD) within 5 years (23). This suggests that PD-MCI represents an early stage of cognitive impairment in PD and a probable transitional stage preceding PDD. Therefore, preventing factors that contribute to the conversion from PD-MCI to PDD is of significant importance in delaying the onset of PDD. Additionally, cognitive dysfunction in Parkinson’s disease is associated with the progression of motor dysfunction (24). Improving cognitive function can contribute to the amelioration of motor symptoms in patients (25), highlighting the importance of early intervention for cognitive impairment.

This study represents the first clinical trial investigating the efficacy of acupuncture therapy for cognitive dysfunction in PD. Currently, research on the treatment of mild cognitive impairment in PD remains limited. The pathogenesis of PD-MCI has not yet been fully elucidated, and western medicine lacks targeted therapeutic approaches. Clinical trials of pharmacological interventions have failed to demonstrate consistent or sustained efficacy. The drugs treating cognitive dysfunction mostly accompanied by adverse effects such as nausea, vomiting, decreased appetite, and other gastrointestinal disturbances (26, 27). Given these limitations, there is an urgent need to explore additional safe and effective therapeutic strategies for PD-MCI.

As a classical therapeutic modality in Traditional Chinese Medicine (TCM), acupuncture has demonstrated clinically meaningful efficacy in the management of post-stroke cognitive impairment (28). Notably, acupuncture exhibits superior therapeutic outcomes to pharmacotherapy for certain psychiatric disorders while avoiding drug-associated adverse effects (29, 30). Acupuncture is a well-established clinical intervention in China. Acupuncture has regionally specific, quantifiable effects on relevant brain structures (31). Acupuncture was found to activate a wide range of brain function areas and promote the neural plasticity of motor and cognitive brain regions neural plasticity (32). Studies has proved that acupuncture can improve cognitive function, restore impaired neurological function, and lower related serum factor levels (8, 33). Recent advanced works evaluate therapeutic effect of acupuncture on human brain through different brain imaging methods, including MRI, fMRI and EEG. Acupuncture may affect brain function by enhancing or inhibiting the connectivity between brain regions, leading to indirect effects on the limb system (5). Scalp EEG and Transformer elucidated the dynamic regulatory effects of acupuncture throughout the treatment process (34). Yu et al. (35) used the EEG decoder to demonstrate that needle insertion can evoke immediate tactile sensations, stimulate peripheral nerves directly and ultimately affect brain regions via central nervous system pathways. Acupuncture increases long-range connections between left and right hemispheres (36). Nierhaus et al. (37) proved that stimulation at acupuncture points is more effective than stimulation at non-acupuncture point locations measured with EEG and fMRI.

In the previous clinical research on acupuncture treatment for PD, we found that acupuncture not only improved Parkinson’s anxiety, but also enhanced the Unified Parkinson’s Disease Rating Scale (UPDRS) scores of patients (38). UPDRS is a commonly used scale for evaluating PD patients’ quality of life, which can objectively evaluate the mental, emotional, daily living ability, motor symptoms and other aspects of PD patients. These findings suggest acupuncture has an overall improvement on the emotional and cognitive functions of Parkinson’s patients. Yan’s study (39) proved that acupuncture can significantly improve the sleep quality of PD patients. Li′s research (40) found that acupuncture treatment for constipation in PD is effective and safe. Xia et al. (41) using electroacupuncture to treat PD combined with depression can improve depressive symptoms, increase the level of BDNF in serum, and the therapeutic effect is superior to that of drug treatment alone. All research above further supports acupuncture’s multimodal benefits for PD non-motor symptoms. Regarding cognitive dysfunction specifically, both clinical studies (42, 43) and preclinical models (44, 45) across various etiologies have consistently shown acupuncture’s therapeutic potential. Therefore, based on the clinical efficacy of acupuncture in treating non-motor symptoms of PD and cognitive dysfunction in previous studies, this study will adopt acupuncture to investigate cognitive dysfunction in PD.

When it comes to acupoint selection, the acupoints located on the head like “Baihui” acupoint and “Shen Ting” acupoint are the most frequently used acupoints for enhancing cognitive performance (46, 47). We use “Si Shen Zhen,” which are next to “Baihui” 1.5 cun bilateral, and add the acupuncture point “Yin Tang” and “Su Liao” to expand the brain stimulus area. The researches showed that acupoints located at the extremities (“Shen Men,” “Hegu,” “San Yin Jiao,” “Taichong”) can stimulate cognitive, emotional brain regions, central nervous system and enhance cerebral blood circulation (48), effectively manage various health conditions (49). Therefore, this study incorporates acupoints from both the head and limbs to achieve holistic improvement.

Recent years have witnessed a growing number of clinical studies investigating acupuncture therapy. However, high-quality clinical research demands more rigorous control designs to examine potential placebo effects in acupuncture interventions. To enhance blinding effectiveness, this study employed a novel sham acupuncture device specifically designed and developed by our research team (15). The device has the advantages of adjustable angle and high stability, which can be applied to both real and sham acupuncture procedures. The special flat-head needle is used on the needle tool, and the appearance of the needle handle is consistent with that of the ordinary acupuncture needle. The device has been extensively utilized in our team’s clinical trials (50–57), with validation studies confirming its excellent blinding efficacy and yielding significant research outcomes.

To comprehensively evaluate acupuncture’s impact on the nervous system, we incorporated serum measurements of NfL and GDNF levels as secondary efficacy indicators. Both NfL and GDNF are closely related to neural cell function. Neural cell degeneration and damage can alter their blood levels. Higher NfL levels indicate more severe axonal degeneration, while more severe cognitive dysfunction correlates with lower GDNF levels. Previous studies have shown that plasma NfL levels are associated with cognitive function in PD patients (58) and can predict clinical conversion of cognitive function (59). It can also reflect changes of cognitive function level (60–62). Therefore, we adopted these indicators to assess acupuncture’s therapeutic effects. Since PD-MCI is difficult to diagnose due to its insidious onset and lack of specific biomarkers, this study also holds clinical value for exploring PD-MCI pathogenesis and improving diagnosis.

This study represents the first randomized, single-blind clinical trial investigating acupuncture treatment for cognitive dysfunction in PD. We employ a sham acupuncture device independently developed by our team as a control, thereby enhancing the credibility of evidence in acupuncture studies. Although some studies in acupuncture research have explored its therapeutic effects on cognitive impairment, no specific acupuncture intervention has yet targeted cognitive dysfunction in PD. Motor and non-motor symptoms in PD often interact and influence each other. Our study simultaneously assessed interventions for motor dysfunction, which may offer new insights into holistic management of PD. Additionally, the study explores the therapeutic mechanisms of acupuncture through clinical biofluid samples.

However, several limitations should be acknowledged. First, all enrolled cases are recruited from a single hospital, which may limit the generalizability of the findings across different regions. Second, minor stimulation may still occur in the sham group. Third, while patient blinding is successfully implemented, practitioners could not be blinded due to the nature of the acupuncture devices used in the study.

This study will provide reliable clinical evidence for the treatment of PD-MCI, thereby improving patients’ survival and quality of life while delaying or preventing its progression to PDD.
